#### Secondary outcome measures

##### Potential impact of intervention on mental health

The potential impact of the exergaming intervention will be assessed by measuring baseline to post-intervention changes in mental health outcomes:

**Depression, anxiety and stress:** Symptoms of depression, anxiety and stress will be measured using the Depression Anxiety Stress Scale (DASS-21). The DASS-21 is a 21-item self-report measure of symptoms of depression, anxiety and stress over the previous week [37]. Higher scores on the DASS-21 indicate a greater severity of symptoms. Assessments will be conducted at baseline, intervention mid-point and post-intervention.

**Positive psychiatric symptoms:** Positive psychiatric symptoms will be assessed at baseline and post-intervention using the Current Community Assessment of Psychic Experiences-Positive Scale (CAPE-P15) [38], a 15-item self-report scale that measures the frequency of psychotic-like experiences over the preceding 3 months. The CAPE-P15 comprises three sub-scales (persecutory ideation, bizarre experiences, perceptual abnormalities), with higher scores indicating more frequent symptomatology.

#### Other measures

##### Exercise intensity

Perceived exertion during exergaming sessions will be measured using the OMNI-Walk/Run Scale of Perceived Exertion assessment for adults [26]. Using the OMNI walking/running pictorial as a visual aid, participants will be asked to rate how hard or easy they perceive the exergaming session to be, based on their perceived levels of exertion. The OMNI-Walk/Run Scale includes numerical categories from 0 to 10, representing a range of exertion levels from “extremely easy” (0) to “extremely hard” (10). OMNI ratings of perceived exertion (RPE) have been validated against objective physiological measures of exercise intensity [26].

In order to ensure that participants do not exceed 85% of their maximum heart rate, as determined using an age-based formula (220−age of participant × 0.85), heart rate monitoring will be conducted at 1-min intervals during the baseline and post-intervention step tests and 10-min intervals during each exergaming session. If, at any time during the step tests, a participant’s heart rate approaches 85% of their maximum heart rate, the test will be discontinued. If this occurs during an exergaming session, a lower intensity game will be used for the remainder of the session.

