### Interventions

#### Exergaming

Participants enrolled in the intervention group will receive a 12-week exergaming programme, delivered by members of the FIT HEART research team who will undergo project-specific training and will be provided with a manual detailing all study procedures. The programme comprises three 30-min exergaming sessions per week for 12 weeks using activity-based games designed to simulate moderate intensity exercise. The exergaming programme will be delivered via Xbox Kinect^TM^ video gaming consoles, with face-to-face supervision of all sessions provided by the FIT HEART research team, nursing staff and unit-based Corrective Services NSW officers. The Xbox Kinect^TM^ system has a large variety of games available, all of which can be played without any equipment (e.g. hand-held controllers). The absence of controllers will minimise the risk of harm to the participants and others. All games to be used in the sessions have been tested by the research team to ensure that a moderate intensity heart rate can be achieved. Selected games include those based on sports, fitness and adventure games (e.g. Kinect Sports, Kinect Adventures, MotionSports Adrenaline, Your Shape: Fitness Evolved, Kinect Rush), dance/rhythm simulation (e.g. Black Eyed Peas Experience, Dance Central) and “party” games (e.g. Raving Rabbids: Alive and Kicking). Each 30-min session will be preceded by a 10-min warm-up utilising one of the lower intensity exergames (e.g. ten-pin bowling, Kinect Joy Ride) and will be followed by a 5-min cool-down, with a choice of stretches designed by an Exercise Physiologist. At 10-min intervals during each exergaming session, participants will be asked to rate their perceived intensity of physical activity using the OMNI-Walk/Run Scale of Perceived Exertion [26] and report the current heart rate displayed on their accelerometer. These measurements will be recorded by the supervising member of the research team. If a participant’s heart rate is not in the moderate intensity range, or if they are seen to be not participating in the game, they will be encouraged to try and increase their intensity or swap to another game.

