#### Primary outcome measures

##### Study feasibility

Feasibility will be measured by the number of participants recruited to the study; participation refusal rates; participant compliance and adherence (i.e. number, length and frequency of intervention sessions attended; compliance with wearing an accelerometer); rates of retention/attrition; occurrence of adverse events (e.g. injury, event related to psychotropic medication, abnormal increase in heart rate during intervention); fidelity of intervention delivery.

Recruitment data will be recorded in screening and enrolment logs, consent forms and study records. Data on intervention compliance, adherence, safety and fidelity of delivery will be recorded on a weekly basis.

In cases where enrolled participants discontinue before completion of the intervention period, reasons for early withdrawal will be documented. Participant discontinuation of the programme due to discharge from the unit will also be documented.

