##### Potential effectiveness of intervention

The potential effectiveness of the exergaming intervention will be assessed by measuring baseline to post-intervention changes in physical health outcomes:

i.Levels of physical activityii.Cardiorespiratory fitnessiii.Measures of cardiometabolic risk

**Physical activity: **Subjective levels of physical activity in the preceding week will be measured at baseline, mid-intervention and post-intervention using the Simple Physical Activity Questionnaire (SIMPAQ), a 5-item tool designed to assess physical activity and sedentary behaviour among people with mental illness [32]. The SIMPAQ measures self-reported activity over the previous week, including time spent in bed, sedentary time, structured exercise participation, and incidental or non-structured physical activity. In a validation study across 23 countries, the SIMPAQ was administered in a diverse sample of psychiatric patients, in both inpatient and outpatient settings, and found to be a reliable and valid tool for the assessment of self-reported physical activity [32].

Objective measures of daily physical activity during the study period will be obtained via accelerometry data. Following the baseline interview, all participants in both the intervention and comparison groups will be issued with an wrist-worn activity tracker (Fitbit® Charge 3) which they will be asked to wear the for the duration of the intervention period and up until the post-intervention assessments, totalling 14 weeks of activity monitoring. The Fitbits will only be worn whilst participants are out of their cell/room and participants will be required to check them in and out each day. Accelerometry data, obtained at 1-min intervals, will include number of steps taken, heart rate, energy (i.e. kilojoule) expenditure, and physical activity intensity as indicated by metabolic equivalent of task (METs) thresholds [33]. All participants will be provided with a weekly summary of their progress which will include their average steps over the preceding week, average heart rate, activity intensity levels (i.e. low, average, high) and average energy expenditure.

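### The heart-rate safety limit is printed without brackets: the formula computes to 33 bpm above the intended 85% limit, and above the age-predicted maximum at every adult age

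*Protocol article*

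**What the plan says.** Under Other measures, Exercise intensity, the protocol article gives a ceiling that participants should not pass: "85% of their maximum heart rate, as determined using an age-based formula (220−age of participant × 0.85"). The article closes the bracket after 0.85 and has no inner bracket around the subtraction.

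Two actions depend on this ceiling:

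- **Step test:** if a participant's heart rate "approaches 85% of their maximum heart rate, the test will be discontinued".
- **Exergaming session:** in the same situation, "a lower intensity game will be used for the remainder of the session".

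On timing, "heart rate monitoring will be conducted at 1-min intervals during the baseline and post-intervention step tests and 10-min intervals during each exergaming session". The Exergaming section adds that at each session check participants "report the current heart rate displayed on their accelerometer". The Participants section admits adults from age 18 and states no upper age.

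**The concern.** The sentence states one limit in words and another in symbols. Multiplication comes before subtraction, so the printed expression takes 85% of the age and subtracts that from 220. It does not take 85% of the difference. The result is far above the worded limit and, for an adult of any age, above the predicted maximum of which it is meant to be 85%.

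This matters because the expression is the article's only numerical definition of an operating rule. A spreadsheet or session sheet that carried it as printed would apply operator precedence, not intent. The rule would then act only when a participant was near or past the predicted maximum, in a population whose raised cardiometabolic risk is the reason for the study. The article is also meant to inform a later randomised trial, so the expression could be carried forward.

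**Working it through.** **Inputs.** The worded limit (85% of maximum heart rate) and the printed formula both come from the Exercise intensity section. The youngest eligible age, 18, comes from the Participants section. The other ages below are illustrative. The age-predicted maximum is taken as 220 − age, the quantity that the formula is plainly built on.

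**Formulas, with a = age in years.**

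- As printed: 220 − a × 0.85 = 220 − 0.85a
- Predicted maximum: 220 − a
- As worded: 0.85 × (220 − a) = 187 − 0.85a

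**Does the printed formula reproduce the worded limit?** It does not under standard precedence. Working strictly from left to right, as if 220 − age were bracketed, does give the worded limit. The missing brackets are therefore the whole of the defect.

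**Differences.**

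- Printed minus worded: (220 − 0.85a) − (187 − 0.85a) = 33 bpm. Age cancels, so the gap is the same for everyone.
- Printed minus maximum: (220 − 0.85a) − (220 − a) = 0.15a, which is positive at every age.

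| Age | Worded limit (bpm) | Printed formula (bpm) | Predicted maximum (bpm) | Printed as % of maximum |
|---|---|---|---|---|
| 18 | 171.7 | 204.7 | 202 | 101.3 |
| 30 | 161.5 | 194.5 | 190 | 102.4 |
| 40 | 153.0 | 186.0 | 180 | 103.3 |
| 50 | 144.5 | 177.5 | 170 | 104.4 |
| 60 | 136.0 | 169.0 | 160 | 105.6 |
| 70 | 127.5 | 160.5 | 150 | 107.0 |

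Example at age 40: printed 220 − 34 = 186; worded 0.85 × 180 = 153; difference 33.

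**Does acting on approach to the limit absorb the error?** Only if the margin were as wide as 33 bpm. At age 40, staff would have to treat 153 as approaching 186. The article gives no margin.

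**The case against.** The best defence is that the text corrects itself. The purpose statement and the stopping rule both express the limit in words, the game-change rule refers back to those words, and the formula appears once, in parentheses, as an explanation. A value above 100% of the maximum cannot be 85% of it, so a careful reader recovers the intended figure. Study staff are trained and "will be provided with a manual detailing all study procedures". The study runs under a full protocol dated November 2018, and sessions began well before the article appeared in June 2022. Neither the manual nor that protocol is shown.

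Most of this stands. It makes a notation slip by far the likeliest explanation. It does not make the printed expression correct, and it cannot show what the unseen manual says.

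Three stronger readings are tempting, and the documents support none of them.

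- **A reader might infer that participants were exercised against the wrong limit.** Nothing in the article indicates this.
- **A reader might infer that the 10-minute session checks are a separate error, because a short excursion can fall between readings.** It can, but the article is stating the purpose of the checks, not guaranteeing their performance. Sessions are also supervised, use games tested beforehand and follow medical screening. Any figure for missed episodes would need assumed episode lengths, and the article gives neither lengths nor frequencies.
- **A reader might infer that time above the limit ought to have been a planned analysis.** The Statistical analysis section promises a separate analysis plan, where such a summary could properly sit. Its absence here is not a fault.

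**Conclusion.** The point holds as a correction to a stated safety threshold. As printed, the formula is 33 bpm above the worded limit at every age. It exceeds the predicted maximum by 0.15 × age: 2.7 bpm at 18, 6.0 at 40 and 10.5 at 70. These results are exact arithmetic and rest only on the usual order of operations and on 220 − age as the predicted maximum.

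The practical consequence is conditional. It arises only if the expression was, or will be, used as printed, and the article gives no evidence of that. No progression criterion in Table 2 refers to the limit, and no sample size or effect estimate is calculated from it. The reason to correct it is that it governs when a step test stops and when a session is eased, and that the repair is trivial.

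**What to change.** 1. Print the limit as (220 − age) × 0.85 in the article and wherever the expression is reused, including the protocol of the future trial.
2. Confirm that the staff manual and any session or step-test sheets carry the bracketed value. If the unbracketed version was ever applied, say so when the results are reported.

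The cost is one pair of brackets and a short document check. No design element, visit or outcome changes.

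As an optional suggestion, separate from the error, minutes above the limit per session could be described from data already being gathered: "Accelerometry data, obtained at 1-min intervals, will include number of steps taken, heart rate, energy (i.e. kilojoule) expenditure". This would complement the feasibility measures, which already list "abnormal increase in heart rate during intervention" as an example of an adverse event. It needs some merging of tracker and session times, and gaps in the tracker record would have to be shown.

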##### General health status

Participants’ perception of their physical health status will be measured during the baseline and post-intervention interviews by asking them to rate their general health as “excellent”, “very good”, “good”, “fair” or “poor”. Self-reported physical health status has been found to be a useful indicator of chronic disease risk and prevalence among the prison population [39].

##### Study participation experience

All participants will be asked about their experience of participation in the study. Specifically, they will be asked whether they enjoyed being part of this study; whether they found wearing the Fitbit comfortable/uncomfortable; if they spent less time sitting while wearing the Fitbit; whether their usual daily routine had changed since being part of the study; if the weekly progress Fitbit information they were provided was useful; and, what things they liked most and least about the study. They will also be given the opportunity to provide comments or suggestions about the project.

### Data management

Data collected at each assessment occasion will be de-identified, with a unique alphanumeric study identifier (ID) created for each participant. All data will be entered into an IBM SPSS database (version 26) for storage and statistical analysis.

De-identified accelerometry (Fitbit) data will be transferred to Fitabase, a research platform that collects and manages data from internet-connected activity devices (Small Steps Labs LLC, San Diego, CA; available at https://www.fitabase.com). Fitabase does not collect personally identifiable information or IP addresses from synced participant devices. Fitbit accounts for each participant will be manually connected to the Fitabase platform and assigned a unique, non-identifiable study ID. All data associated with the Fitbit device will be linked to the allocated study ID in the Fitabase platform.

All paper records (i.e. consent forms, surveys, compliance and adherence logs, accelerometer register, clinical data) will be stored in locked filing cabinets located in the JHFMHN Research Unit. Consent forms and referral forms (see *Safety monitoring and reporting*) will be stored separately from hardcopies of the surveys. There will be restricted access to files, with access limited to project staff with direct involvement in the study. Paper records will be retained in line with *Ministry of Health Policy Directive PD2009_057 Records Management-Department of Health and the State Records Authority NSW General Retention and Disposal Authority–Public Health Services: Administrative Records-GDA21*.

Electronic files will be saved in limited-access folders, access to which requires a JHFMHN log-in, password and specific permissions. Data will be stored for five years from date of first publication of the data, in line with the recommendations of the National Health and Medical Research Council. After this time, all electronic files will be deleted and paper files shredded. All data will be deleted from Fitabase on completion or withdrawal from the project. Ninety days after the completion of data collection, Fitabase will remove the project from their data management system, disassociate the data from the project, and begin to remove access to the data by deleting it from its servers and backup systems.

### Statistical analysis

A detailed Statistical Analysis Plan will be developed and agreed upon by the project team prior to the commencement of data analysis.

#### Quantitative data

Quantitative feasibility outcomes will be reported descriptively and narratively. Rates of recruitment, retention, protocol adherence/compliance, intervention fidelity and adverse events will be presented as frequencies and proportions. Participants recruited to the study in the initial wave (January–March 2020), prior to the suspension of recruitment during the COVID-19 outbreak in NSW (March–June 2020), will be replaced by new participants to achieve the target sample size and will have their data excluded from the final analysis.

Primary and secondary outcomes will be analysed descriptively and presented for the overall sample and by group. Means, standard deviations and ranges, or medians and interquartile ranges, as appropriate, will be reported for continuous data, and frequency counts and proportions for categorical data, with associated 95% confidence intervals. Missing data for each of the primary and secondary outcome measures will be described using descriptive statistics. Missing data will not be replaced or imputed.

As this pilot study primarily aims to determine the feasibility of conducting a future definitive intervention trial and is not powered for statistical hypothesis testing, statistical analysis of the potential effectiveness of the intervention will not be performed on the clinical outcome data. Physical activity, cardiorespiratory fitness, and cardiometabolic risk data collected at each timepoint will be summarised descriptively for each group. Whilst between-group statistical comparisons will not be undertaken, post-intervention differences between groups will be reported using estimated mean differences and 95% confidence intervals, where appropriate.

Perceptions of exercise intensity, general health status and the study experience will be reported descriptively and narratively. All analyses will be performed using IBM SPSS software (Version 27) [40].

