**Methods:**

This non-randomised, two-arm pilot study will employ a pre-test/post-test parallel group design, comparing the exergaming intervention with a “routine treatment” control. Two high-secure, sub-acute wards in the Long Bay Hospital Mental Health Unit will be non-randomly allocated to either the exergaming intervention or the “routine treatment” control group.

The intervention group will receive a 12-week programme comprising three 30-min exergaming sessions per week using various Xbox Kinect^TM^ activity-based games designed to simulate moderate intensity exercise. The “routine treatment” group will continue to receive the standard model of care delivered by the Justice Health and Forensic Mental Health Network. Accelerometers will be distributed to all participants to collect daily energy expenditure, number of steps taken, intensity of physical activity and heart rate data throughout the study.

The primary outcomes are (1) intervention feasibility and acceptability, and (2) baseline to post-intervention changes in physical health outcomes (levels of physical activity; cardiovascular fitness; clinical measures of cardiometabolic risk). Secondary outcomes are baseline to post-intervention changes in mental health outcomes (depression, anxiety, stress, positive psychiatric symptoms). Outcomes will be assessed at baseline, mid-intervention, and post-intervention.

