#### Safety monitoring and reporting

Safety monitoring and reporting procedures will be aligned with the requirements for clinical trials conducted in Australia [44] and in NSW Public Health Organisations in particular (*Office for Health and Medical Research Policy Directive PD2017_039-Safety Monitoring and Reporting for Clinical Trials Conducted in NSW Public Health Organisations*).

The occurrence of any unexpected or adverse events during the study period, irrespective of whether they may be causally related to the study, will be recorded. Daily monitoring of adverse events will be conducted via brief interviews with staff and patients and health record review. An adverse event that meets the criteria for a serious adverse event (SAE) will be reported to all relevant ethics committees: JHFMHN Human Research Ethics Committee (HREC), Aboriginal Health & Medical Research Council (AH&MRC). SAEs occurring after a subject has withdrawn from, or completed participation in, the study will not be reported unless the investigators believe that the event may have been caused by the study intervention or a protocol procedure. Investigators will determine potential causality based on whether there is a temporal relationship to participation in the study, as well as whether the event is unexpected or unexplained given the participant’s previous medical conditions and current medications.

Prior to each exergaming session, the Dynamic Appraisal of Situational Aggression (DASA) will be completed for each participant. The DASA is an instrument designed to assess the risk of imminent violence (i.e. within 24 h of administration) in psychiatric patient populations [45]. Any participant that presents a risk of aggression/violence will be excluded from the session for that day and will recommence sessions subject to re-appraisal of risk.

In cases where a participant discloses, or research staff are alerted to, a new and/or unmanaged health condition during the course of the study, a referral form will be completed and handed over to clinical staff at the study site for appropriate follow-up. Information alerting participants to this referral process is included in the PIS.

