## Study status

Recruitment and data collection commenced in January 2020, but was put on hold in March 2020 in response to the suspension of AH&MRC HREC approval for face-to for face-to-face data collection due to the emerging COVID-19 outbreak in NSW. Following a lifting of the suspension, recruitment recommenced in June 2020 and is anticipated to end in December 2022. Due to the nature of the intervention, requiring face-to-face data collection, there were no variations to the protocol with respect to the study design and methods. The study is being conducted in accordance with version 3.0 of the FIT HEART study protocol (14 November 2018).

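### The blanket exclusion of the January–March 2020 wave should not extend to its consent, adherence-to-pause and adverse-event data

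*Protocol article*

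**What the plan says.** The rule is in the protocol article under Statistical analysis, Quantitative data. It applies to "Participants recruited to the study in the initial wave (January–March 2020), prior to the suspension of recruitment"; these people "will be replaced by new participants to achieve the target sample size and will have their data excluded from the final analysis". The sentence immediately before it sets out the feasibility reporting: "Rates of recruitment, retention, protocol adherence/compliance, intervention fidelity and adverse events will be presented as frequencies and proportions". Nothing in the paragraph limits the exclusion to particular outcomes, and no reason is given beyond the reference to the suspension.

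Other sections bear on it:

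- **Abstract, Methods:** "The primary outcomes are (1) intervention feasibility and acceptability, and (2) baseline to post-intervention changes in physical health outcomes". The Strengths and limitations section also names feasibility and acceptability as the main aim.
- **Study feasibility:** "Feasibility will be measured by the number of participants recruited to the study; participation refusal rates; participant compliance and adherence". The same sentence adds retention, adverse events and fidelity, and the section asks for the reason to be noted whenever someone stops early.
- **Safety monitoring and reporting:** "any unexpected or adverse events during the study period, irrespective of whether they may be causally related to the study, will be recorded".
- **Study status:** data collection began in January 2020, stopped in March when ethics approval for face-to-face work was suspended, and resumed in June 2020. Across that pause, "there were no variations to the protocol with respect to the study design and methods".
- **Progression criteria, Table 2:** the go/amend/stop decision uses percentages of eligible patients (consent) and of recruited participants (retention, adherence, accelerometer wear).

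**The concern.** Feasibility is the first-listed primary outcome. Its components are events that the initial wave could supply before the pause: who was approached, who agreed or refused, what was attended and worn, why people stopped, and what harms occurred. Followed as written, the rule takes all of this out of the final analysis for everyone enrolled in that period, and out of the Table 2 denominators.

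Two things are at stake. First, the reported adverse-event rate would omit events in enrolled participants because of a later administrative pause that has no bearing on whether those events occurred. Secondly, the decision on a definitive trial would rest on consent and adherence percentages from which part of the experience has been removed. For consent, the wording does not even make clear which part: it covers participants recruited, and does not say what happens to eligible patients who refused in the same months.

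**Working it through.** **1. The plan's own figures.** Sample size section: 30 per arm, so 2 × 30 = 60. With the 20% attrition allowance, 60 × (1 − 0.20) = 48 completers, and 48/60 = 80.0%, which is exactly the green threshold for retention. No power calculation was made and the size of the initial wave is not given, so there is no published rate to reproduce.

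**2. Could the initial wave reach the endpoint?** Table 1 puts baseline at week 0 and the post-intervention assessment at weeks 13–14. Taking the earliest possible baseline as 1 January 2020:

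- 12 weeks later is 25 March 2020
- 13 weeks later is 1 April 2020
- 14 weeks later is 8 April 2020

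Data collection stopped in March 2020, so on this schedule nobody in the wave could attend the planned final assessment. Non-retention was imposed from outside.

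**3. Which data does that invalidate?**

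| Data from the initial wave | Depends on weeks 13–14? | Exclusion defensible? |
|---|---|---|
| Baseline-to-post change | Yes | Yes |
| Table 2 retention | Yes | Yes |
| Screening, consent, refusal | No | No |
| Attendance and accelerometer wear to the pause | No | No |
| Reasons for stopping | No | No |
| Adverse events | No | No |

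The Study status section reports the same design and methods before and after the pause, so the article offers no ground for treating the last four rows as invalid.

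**4. Share of participants removed.** Let k be the wave size. This is an assumption; 30 is one full bed complement (2 units × 15). The share of all recruited is k/(60 + k):

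- k = 5: 5/65 = 7.7%
- k = 15: 15/75 = 20.0%
- k = 30: 30/90 = 33.3%

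**5. Consent rate (green ≥ 50%, amber 30–49%).** Assume 60 of 120 eligible patients consent after the restart, 60/120 = 50.0%. Adding an assumed initial wave, consenters and refusers together:

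- 5 of 15: 65/135 = 48.1%
- 10 of 30: 70/150 = 46.7%
- 10 of 15: 70/135 = 51.9%
- 20 of 30: 80/150 = 53.3%

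The rate can move either way. If the rule is read literally, and the 10 consenters of 15 are dropped while their 5 refusers stay, the rate is 60/(120 + 5) = 48.0%, against 51.9% with everyone counted.

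**6. Retention, to show why it should be a sensitivity figure.** Counting all k as recruited but not retained, from a start of 48/60:

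- k = 1: 48/61 = 78.7%
- k = 5: 48/65 = 73.8%
- k = 9: 48/69 = 69.6%

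From a start of 54/60 = 90%, k = 5 gives 54/65 = 83.1%, still green. The result therefore depends on two unknowns, the wave size and the retention after restart. By step 2, the added losses reflect the suspension.

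**The case against.** The strongest defence is that the wave was cut short by a suspension of ethics approval, that the exclusion is by calendar date and so does not select on outcomes, and that it was published in June 2022, while recruitment was expected to run to December 2022 and before a detailed analysis plan had to be agreed. All of this stands for pre/post change and for retention. It does not reach consent, adherence to the pause or adverse events, which do not depend on the missed assessment.

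The term final analysis could also be read as the clinical outcome analysis alone. That is possible, but the sentence sits in the feasibility paragraph and its wording is unrestricted; if the narrow meaning is intended, the text should say so.

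A reader might infer more than the documents support:

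- **That the rule makes feasibility look better than it was.** Not shown. The wave size is unstated, consent can move either way, and the retention illustration falls out of green at once only because it starts on the boundary.
- **That adverse events are lost.** Too broad. Recording, and reporting of serious events to the ethics committees, apply regardless of the analysis set; only the reported rate is affected.
- **That the exclusion hides the access problems the plan itself foresees.** The Strengths and limitations section speaks of lockdowns for staffing or security reasons. Those can still occur, and be captured, after June 2020.
- **That the statement of no variation contradicts the exclusion.** That statement concerns design and methods. The rule must postdate the 2018 protocol version, but an external interruption could not have been foreseen, and nothing suggests that results drove it.
- **That initial-wave patients all completed step tests, blood sampling and sessions.** The article says only that recruitment and data collection had begun.

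**Conclusion.** The point holds in a limited form. The exclusion is wider than its evident justification: the suspension explains the absence of weeks 13–14 data and nothing else. Applied as written, the rule removes consent results, adherence and accelerometer wear to the pause, reasons for stopping and adverse events from a primary outcome and from the reported safety rate, although they were collected under unchanged methods. Leaving the wave out of pre/post summaries and the retention criterion is reasonable.

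The size and direction of the effect on Table 2 cannot be stated. The illustrations rest on assumed wave sizes of up to 30 and on an assumed 60 of 120 consenting after restart; they show only that a threshold could be crossed. The conclusion does not depend on them. It rests on the unqualified wording, its place in the feasibility paragraph, and the article's own definition of feasibility.

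**What to change.** Reword the rule, and carry it into the analysis plan, along these lines:

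- Participants recruited in January–March 2020 are left out of the baseline-to-post outcome summaries and of the Table 2 retention criterion only.
- The screening and consent rate includes this wave, consenters and refusers alike.
- Adverse-event reporting includes this wave.
- Adherence and accelerometer compliance up to the date of suspension, and reasons for discontinuation, are reported for this wave separately and combined with the later cohort, where the data are held.
- The flow diagram shows the wave, its size and the reason for interruption.
- The Table 2 retention decision uses the post-restart cohort, with the all-recruited figure shown as a sensitivity result.

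Keep the replacement participants; the target of 60 is unaffected. Acceptability surveys are given only after the intervention or at early discontinuation, so few may exist for this wave and no rule need depend on them. The Data management section provides for deletion of Fitabase records on completion or withdrawal, so the sponsor should confirm now which accelerometer data from this wave survive.

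The cost is a few sentences, one extra column in the tables, and the possibility that some reported rates are slightly less favourable.
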